## Accountability Procedures for the Study Investigational Drugs

Clinical investigators will issue a prescription for each enrolled patient per USP 1168 and State and Federal Law. Buderer Drug Co. will schedule, prepare, package, label and ship clinical trial materials to participating facilities.

The study drug will be kept in the institutional Investigational Drug Pharmacy. Upon receipt of drug orders, and documentation of negative pregnancy test (for women of childbearing age), the pharmacist will dispense enough suppositories for a full cycle (5 days). When dosing visits are done as telemedicine, the Institutional Pharmacy will ship the suppositories to the patient’s home, per institutional guidelines.

## Assessment of Subject Compliance with Self Administration of Artesunate Suppositories

Eligible patients will have clinic or telemedicine visits scheduled at weeks 0, 2, and 4 for a urine pregnancy test (if female) and dosing. Once documentation of a negative pregnancy test is obtained (women of childbearing potential only), the patient will receive 5 doses of Artesunate for the respective treatment cycle. They will receive instructions on how to apply the suppositories and will apply the first dose of Artesunate during this visit. At each dosing visit, the study team will confirm contact information where they can be reached the following week. At dosing visits 2 and 3, if done in person, patients will have an anoscopy to assess the dentate line, and document any adverse events. For telemedicine visits, the investigator and/or study coordinator will review the Symptom Diary with the patient anddocument AEs. The Investigator will grade and determine causality to the study medication. Patients will have an in-person additional anoscopy and HPV genotyping at week 6 (+/- 1 week).

Patients will be monitored throughout the study for both known potential risks and for unexpected risks. During office visits, patients will be monitored specifically for any signs of:

- - - Symptoms of itching, burning, pain, warmth, or tenesmus
    - Signs of skin breakdown including erythema, blistering, desquamation, ulceration or bleeding
    - Neurologic symptoms
    - Unexpected adverse events

Subjects will be given diary cards to record local and general signs and symptoms most likely to occur between office visits. The diary cards will be collected, signs and symptoms verified, and inserted into the CRF at each subsequent visit.

# BIOMARKER, CORRELATIVE, AND SPECIAL STUDIES

- Downgrade in AIN 2/3 to AIN 1 or no AIN by HRA evaluation
- Decrease in HPV genotype testing by PCR of anal pap test sample—optimally to undetectable levels of HPV at week 40 of follow-up.
- Creation of tissue bank of specimens obtained from patients.

Please note that the highlighted tests above are depicted in the flow diagram and timeline in the schematic diagram on the next page.

##
[figure not shown]

[figure not shown]

[figure not shown]

**Screening visit—HRA, anal pap, HPV genotyping**

**Week 0 (Cycle 1)**

Artesunate suppositories

A

**Week 2 (Cycle 2)**

Artesunate suppositories (Anoscopy)

**Week 4 (Cycle 3)**

Artesunate suppositories (Anoscopy )

**Week 16**

Assess for residual disease: HRA + biopsy + pap smear + HPV genotyping

Some improvement observed:

- Lesion size by office HRA
- AIN grade reduction (Biopsy, pap smear)

No improvement

Ablation in OR

**Week 28**

Assess for residual disease: HRA + biopsy + pap smear + HPV genotyping

No detection of AIN2/3 lesion by biopsy + anal pap smear

Detection of AIN2/3 lesion by biopsy + anal pap smear

Ablation in OR

**Week 40**

Assess for relapsing disease: pap smear and if clinically indicated HRA + biopsy + HPV genotyping

**Week 6**

(Follow-up Anoscopy )

##

## Collection of Specimens

Anal brushing tests (a.k.a. cytology brushings) will be obtained for both standard of care cytopathological evaluation and also to create a tissue bank for future analysis studies.

## Pathology slides (Biopsy and resection tissue samples)

Representative diagnostic hematoxylin and eosin slides cut from FFPE blocks of  diagnostic biopsy at study entry and post-artesunate biopsy and/or therapeutic resection/ablation will be sent by participating sites to JHU for centralized adjudication by an independent pathologist, blinded to outcomes.  We will evaluate the histologic ‘context’ in subject-matched tissue specimens obtained before, during, and after treatment. Whenever possible, additional recuts of the paraffin-embedded blocks will be sent to JHU for additional staining and analyses.

## Handling of Specimens

Regular anal pap testing and HRA biopsies will be submitted to Pathology as per standard hospital protocol to evaluate for pathological diagnosis. Samples for HPV genotyping will be sent to Atila Biosystems. Anal brushes and blood specimens will be banked in [name] lab at Johns Hopkins. Anal brushes and blood specimens collected at the University of Wisconsin will be processed and stored locally and shipped to JHU in batch.

## Sites Performing Correlative Studies

Johns Hopkins Hospital

Pathology Laboratories – JHU, UWM

Atila Biosystems

Department of Clinical Pharmacology

# STUDY eVALUATION

Baseline evaluations are to be conducted within 4 weeks prior to start of protocol therapy. In the event that the patient’s condition is deteriorating, laboratory evaluations at the discretion of the physician should be performed within 48 hours prior to initiation of the next cycle of therapy.

Please refer to Study Calendar, Appendix A.

## Description of Study Visits

All clinically relevant data collected during the study procedures must be recorded first in the patient file. These data will then be transcribed into the CRF. All visits will be outpatient visits.

At the initial screening visit, in addition to undergoing a standard of care high-resolution anoscopy evaluation, we will obtain anal cytology brush specimens for HPV genotyping, Subjects with biopsy-confirmed AIN2/3 will be enrolled into treatment cohorts as previously described (see table). Subjects who underwent HRA with biopsy and pap smear within the 3 months preceding the screening visit will not need an additional biopsy and anal pap smear for study entry.

## Visit intervals

Study visits and study procedures will be carried out within the timeframe outlined below.

Table 1**: Visit/procedures timeline**

| **Screening visit** | **Biopsy diagnosis within the 3 months prior to the visit may be accepted for study entry**  **HIV testing and CD4 counts within the 6 months prior to study entry may be accepted for study entry** |
| --- | --- |
| **Week 0** | 4 weeks +/- 2 weeks after the screening visit  Questionnaire/phone f/u 2-7 days after last day of dosing |
| **Week 2 – may be done as televisit** | 2 weeks +/- 1 week  Questionnaire/phone f/u 2-7 days after last day of dosing |
| **Week 4 – may be done as televisit** | 4 weeks +/- 1 week  Questionnaire/phone f/u 2-7 days after last day of dosing |
| **Week 6** | 6 weeks +/- 1 week |
| **Week 16** | 16 weeks +/- 2 weeks |
| **Week 28** | 28 weeks +/- 2 weeks |
| **Week 40** | 40 weeks +/- 2 weeks |
| **Excision (if needed)** | Can take place any time after week 16 HRA |

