## Secondary Objectives

- - 1. To measure the effect of intra-anal topical Artesunate administration determined by pathology, based on the regression of AIN2/3 at study weeks 16, 28, and 40. Regression defined as either AIN1 or no AIN lesion detected by HRA/biopsy and anal cytology.
    2. To evaluate the clearance of HPV as assessed by HPV genotype testing of cytologic specimens.

1.2.3 To create a tissue bank for future studies.

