# PATIENT SELECTION

## Eligibility Criteria

- Age ≥ 18 years.
- Biopsy-confirmed high-grade anal dysplasia (AIN 2, AIN 3, HSIL) by HRA. This includes patients who are newly diagnosed with AIN 2/3 as well as those who have recurrent AIN 2/3 after medical therapy or surgical therapy.
- Female of childbearing potential: negative urine pregnancy test.
- Adequate contraceptive use for males and females of reproductive potential.
- Able to provide informed consent.
- Patients who have the ability to collaborate with planned follow-up (transportation, compliance history, etc.).
- Patient who have and have not been immunized with the HPV vaccine.
- Weight ≥ 50 kg.
- Life expectancy > 2 years.

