# APPENDIX A: STUDY CALENDAR

Baseline evaluations are to be conducted within 4 week prior to start of protocol therapy. In the event that the patient’s condition is deteriorating, laboratory evaluations should be performed per they study physician’s discretion within 48 hours prior to initiation of the next cycle of therapy.

| **Surveillance Period** | | | | | | | | |
| --- | --- | --- | --- | --- | --- | --- | --- | --- |
|  | Screen | Cycle 1 (wk 0) | Cycle 2 (wk 2)1 | Cycle 3 (wk 4)1 | Wk 6 | Wk 16 | Wk 28 | Wk 40 |
| Artesunate |  | X | X | +/- |  |  |  |  |
| Informed consent | X |  |  |  |  |  |  |  |
| Demographics | X |  |  |  |  |  |  |  |
| Complete History | X |  |  |  |  |  |  |  |
| Physical exam | X |  |  |  |  |  |  |  |
| Vitals signs | X | X | X2 | X2 | X | X | X | X |
| Urine hCG (if female) | X | X | X3 | X3 |  |  |  |  |
| HIV test with reflex CD4 count | X |  |  |  |  |  |  |  |
| AE diary cards |  | X |  |  |  |  |  |  |
| Anal pap | X |  |  |  |  | X | X | X |
| Anal brushes | X | X | X2 | X2 | X | X | X | X |
| Anoscopy | X |  | X2 | X2 | X | X | X | X |
| HRA | X |  |  |  |  | X | X | X |
| HPV testing | X |  |  |  | X | X | X | X |
| Bloods for banking | X |  |  |  | X | X | X | X |

+/-: The patient may or may not get the Artesunate or undergo anal pap test depending on the dosing schedule they are assigned to.

***Please note that anoscopy is part of the HRA evaluation. Anoscopy without concurrent HRA will be used to evaluate for any toxicity to the local tissue at the dentate line at the week 6 visit.

****Participants who are on the 2 cycle dosing schedule will still be seen on cycle 3 week 4 but will not have a urine hCG test or get dispensed Artesunate.

1may be done as telemedicine visits

2will be obtained at in-person visits only

3for telemedicine dosing visits, the patient will do a home pregnancy test and will send a picture to the study team, along with an attestation of negative pregnancy test.

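### The biopsy and cytology from which regression is measured can be about 19 weeks old at first dose, against a stated 4-week baseline window, and no rule requires the lesion to be still visible

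*Protocol*

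**What the plan says.** Two places set a baseline window. Section 8 states "Baseline evaluations are to be conducted within 4 weeks prior to start of protocol therapy", and the study calendar in Appendix A repeats it.

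Two other places allow more. Table 1 (section 8.2) states "Biopsy diagnosis within the 3 months prior to the visit may be accepted for study entry" and puts week 0 at "4 weeks +/- 2 weeks after the screening visit". Section 8.1 says that patients with HRA, biopsy and pap in the 3 months before screening "will not need an additional biopsy and anal pap smear for study entry". Table 1 names only the biopsy; section 8.1 extends the waiver to cytology.

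The endpoint depends on these specimens. Section 1.2 gives the definition: "Regression defined as either AIN1 or no AIN lesion detected by HRA/biopsy and anal cytology", at weeks 16, 28 and 40. Section 7.2 makes the diagnostic biopsy at entry the pre-treatment specimen for central pathology. Section 14.3 analyses regression as a proportion with a 95% confidence interval. Section 5.2 adds that complete resolution of high-grade lesions in a cohort stops escalation and moves the trial into the 12-patient expansion.

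**The concern.** The 4-week window and the 3-month allowance cannot both govern the qualifying biopsy, and the protocol does not call one an exception to the other. Even without the allowance, a biopsy taken at screening can fall outside 4 weeks, because week 0 may be 6 weeks later.

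This matters because there is no concurrent control. Any change between the qualifying biopsy and week 0 is included in the change read at week 16. If a lesion disappears in that gap and nobody notices, the patient enters as AIN2/3 and is counted as a regression. That error can only raise the regression proportion. It would carry into the comparison with the HRA database planned in section 10.1 and could contribute to the resolution rule in section 5.2, where cohorts start at 3 patients.

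**Working it through.** **Inputs**
- Age of a pre-screening biopsy at screening: up to 3 months (sections 8.1 and 8.2), taken as 91 days = 13 weeks.
- Screening to week 0: 4 ± 2 weeks, so 2 to 6 weeks (Table 1).
- Week 0 to the week 16 visit: 16 ± 2 weeks, so at most 18 weeks (Table 1).
- Stated baseline limit: 4 weeks before first dose (section 8, Appendix A).

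**Formulas**
- Biopsy age at first dose = age at screening + screening-to-week-0 interval.
- Longest biopsy-to-week-16 interval = largest biopsy age at first dose + 18.

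| Basis | Biopsy age at week 0 (weeks) | Longest interval to week 16 visit (weeks) |
|---|---|---|
| Stated 4-week rule | at most 4 | 4 + 18 = 22 |
| Biopsy taken at screening | 2 to 6 | 6 + 18 = 24 |
| Biopsy 3 months before screening | 13 + 2 = 15, 13 + 4 = 17, or 13 + 6 = 19 | 19 + 18 = 37 |

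The 4-week limit is not reproduced by the visit schedule. A biopsy at the edge of the allowance exceeds it even at the shortest screening interval (15 weeks). At the longest, the excess is 19 − 4 = 15 weeks, and the interval to week 16 is likewise 37 − 22 = 15 weeks longer. How 3 months is counted hardly matters: 90 or 92 days gives 18.9 or 19.1 weeks at week 0, and 84 days gives 18.0 (36.0 to week 16).

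**Does anything else cap the age or confirm the lesion?**
- Section 4.1 asks for treatment within 4 weeks of registration. That clock does not start at the biopsy.
- Everyone has an HRA at screening (sections 8.1 and 8.3.7, Appendix A). No eligibility rule requires it to show the qualifying lesion.
- Section 3.2 excludes low-grade disease found by HRA and condyloma that hides HSIL. Neither clause says what happens when the screening HRA shows no lesion.

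**Size of the effect**

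The bias depends on two quantities: the share of patients entered on a pre-screening biopsy, and the extra proportion of their lesions lost unnoticed before week 0. The protocol gives neither, so the bias cannot be computed. What follows from the design alone is the weight of one patient. A patient counted as a regression who would otherwise have been a non-regression moves the proportion by 1/12 = 8.3 percentage points in the expansion cohort and by 1/3 = 33 points in a cohort of 3.

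**The case against.** The best defence is that the 3-month allowance is deliberate. It appears twice, stands beside a 6-month allowance for HIV and CD4 results, and matches the 3-month HRA and biopsy interval that the synopsis calls standard of care. Sparing a repeat anal biopsy is reasonable in a Phase I safety trial. This stands as a reason to keep the allowance. It does not remove the conflict, since no passage names it as an exception and the 6-week limit for week 0 breaks the 4-week rule by itself.

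Second, there are safeguards: the universal screening HRA, the low-grade exclusion, and a week 16 branch in the schema that judges lesion size and so presumes a lesion was seen. These reduce the risk but stop short of a persistence rule.

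Third, regression is secondary and descriptive, and the DLT-based definition of the MTD does not use it. With 12 patients the interval is wide anyway: 6 of 12, taken as an example, has an exact 95% interval of about 21% to 79%. This limits the weight of the point. But imprecision does not excuse an avoidable one-directional error, and the resolution rule in section 5.2 gives regression a route into dose selection.

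Fourth, spontaneous regression after week 0 is credited to the drug in any single-arm trial, and loss of a lesion through the biopsy itself also affects biopsies taken at screening. Both are correct. Only the extra loss due to the older biopsy belongs to this point.

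A reader might also infer that patients treated between the qualifying biopsy and week 0 are admitted and counted as regressions. The documents do not support that. Section 3.1 admits "those who have recurrent AIN 2/3 after medical therapy or surgical therapy", which most naturally means AIN2/3 confirmed after that therapy, and section 8.3.3 records previous therapies at screening. What remains is that the order of biopsy and treatment is not stated outright.

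**Conclusion.** The contradiction holds. The qualifying histology and cytology can be about 19 weeks old at first dose (18 if 3 months means 84 days), and a biopsy taken at screening can be 6 weeks old, against a stated 4. On the same visit window, the week 16 assessment can come about 37 weeks after the biopsy instead of 22. These figures rest only on the protocol's own windows.

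The consequence is a possibility, not a demonstrated bias: a lesion lost before dosing can be counted as an artesunate regression. It would be tempting to say that the regression proportion is inflated by some number of percentage points. The documents give no pre-dose regression rate and no share of patients entered on older biopsies, so no such figure is supportable. Nor does the point show that the DLT-based MTD is wrong; the only link to dose selection is the resolution rule in section 5.2. The point should be corrected because the direction of the error is known and the remedy is cheap.

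**What to change.** 1. Reconcile sections 8 and 8.1, Table 1 and Appendix A into one baseline rule that states explicitly which window applies to the biopsy and pap and which to other evaluations, and that agrees with the permitted screening-to-week-0 interval.
2. If the 3-month allowance is kept, require the screening HRA, already performed in everyone, to document a persisting lesion at the qualifying site. State that the qualifying biopsy must post-date any prior AIN treatment.
3. Record the biopsy-to-week-0 interval on the CRF. Report regression with a descriptive sensitivity analysis that excludes patients entered on a pre-screening biopsy. A split at 4 weeks would serve less well: screening biopsies can be up to 6 weeks old, so it would not isolate the older biopsies, and it would divide about 12 patients into groups too small to read.

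The cost is protocol wording, one date field and one descriptive analysis, with no added procedure. The downside is that a few patients whose lesion is no longer visible would be screened out.

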## Examinations, Evaluations, and Procedures

**8.3.1 Vital signs**

Sitting blood pressure and heart rate will be measured both prior to each procedure and drug administration. Additional investigation may be added at the discretion of the investigator.

**8.3.2 Demographics/Medical history**

The patient’s age, weight, height, and ethnicity will be ascertained at the screening visit. Information will be collected on the patient’s past significant medical history including tobacco exposure, sexual practices, HIV status, contraceptive use, total and current number of partners, and current medical status.

**8.3.3 History of HPV-related disease**

The following information will be noted at the screening visit:

- Month/year of detection of AIN lesions, cervical, or vulvar lesions.
- Details of previous therapies.

**8.3.4 HIV test**

If positive HIV test, then will obtain CD4 count, if the patient has not had one within the last 6 months. Those patients with a CD4 count > 200 will be included in this study.

**8.3.5 Urine sample**

A urine pregnancy test for HCG will be performed in women of childbearing potential prior to each suppository administration.

**8.3.6 ANOSCOPY**

Anoscopy will be performed at the week 2 and week 4 dosing visits (if dosing visits take place as in-person visits) and/or within 2 week after the last administration of the artesunate suppository to evaluate for mucosal irritation from suppository administration.

# 8.3.7 HIGH-RESOLUTION ANOSCOPY examination

Patients will undergo serial HRA examinations; at the screening visit, and at weeks 16, 28, and 40. Exfoliated cell samples will be obtained using at the time of HRA, for anal cytology, HPV typing, and for tissue bank storage. Anoscopy will be performed and the anal canal will be visualized with a Zeiss colposcope. Serial applications of 5% acetic acid followed by Lugol’s solution into the anal canal will be analyzed by an anoscope to identify vascular abnormalities. Biopsies will be obtained with an endoscopic cold forceps biopsy. Specimens will be stored in formalin. Specimens for HPV genotyping will be processed by the Atila Biosystems. Specimens for the tissue bank will be directed to the biorepository owned by [name], where they will be processed and cryopreserved for analysis in future studies.

# 8.3.8 HRA, BIOPSY, AND SURGICAL ABLATION

At weeks 16 and 28, if there is residual disease visualized by HRA, patients will undergo repeat HRA with surgical ablation in the operating room by fulguration. If not obtained in the HRA in the office prior to ablation in the operating room, biopsies will be obtained prior to fulguration and resection specimens will be taken fresh to surgical pathology. If possible, a frozen section will be performed to confirm the presence or absence of AIN2/3. The frozen section block will be banked at –70°C in [name] biorepository at Johns Hopkins.

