| **Statistical Methods**:   1. **Definition of primary outcome/endpoint:** This is a Phase I modified 3 + 3 design, in which the MTD will be identified. 2. **Definition of secondary outcomes/endpoints:**  - Downgrade in AIN 2/3 to AIN 1 or no AIN - HPV genotype testing—optimally to undetectable levels of HPV at week 40 of follow. - Creating of tissue bank for future studies.   **Analytic plan for primary objective:** This is a Phase I modified 3 + 3 design, in which the MTD will be identified. Based on previous studies of rectally administered Artesunate for the treatment of malaria, the safety profile demonstrates a low probability of dose limiting toxicity in children, as well as adults. The initial dose will be a 200 mg suppository administered in cycles of 5 daily doses at weeks 0 and 2. Dose escalation will proceed with a 3 + 3 design with the safeguard of an integrated de-escalation schema. At the MTD, an expansion cohort of 12 patients will be included.  Note: Each cycle = 5 days   | **Dose Escalation Design** | | | | | | --- | --- | --- | --- | --- | | **Cohort** | **Dose (mg)** | **Number of Treatment Cycles** | **Designated Weeks of Artesunate Administration** | **Number of patients** | | **I** | 200 | 2 | 0, 2 | 3 | | **II** | 200 | 3 | 0, 2, 4 | 3 | | **III** | 400 | 2 | 0, 2 | 3 | | **IV** | 400 | 3 | 0, 2, 4 | 3 | | **V** | 600 | 2 | 0, 2 | 3 | | **VI** | 600 | 3 | 0, 2, 4 | 3 |   ***According to the standard of care clinical practice, a postoperative visit will be done 4 weeks after ablation, i.e. either on week 20 or on week 32   1. **Analytic plan for secondary objectives:**     1. For the dichotomous variables of regression of AIN 2/3, counts, percents and 95% confidence levels will be calculated.    2. HPV viral genotyping will be assessed to determine when HPV viral load will become undetectable.    3. Tissue bank of specimens for future studies. 2. **Sample size justification:** In this phase I dose escalation trial, 6 dose levels will be considered for a total sample size of 36-60 patients with a target dose limiting toxicity (DLT) of < 18%. |
| **Funding, Regulatory, and Feasibility Issues:**  Frantz Viral Therapeutics will supply the Artesunate suppositories at no cost. The suppository will be obtained from an off-site pharmacy (Buderer Drug Company).  Buderer Drug Company will ship suppositories to the Johns Hopkins Hospital Investigational Drug Pharmacy for each patient enrolled in the study. |

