**Week 16**

Assess for residual disease: HRA + biopsy + pap smear + HPV genotyping

Some improvement observed:

- Lesion size by office HRA
- AIN grade reduction (Biopsy, pap smear)

No improvement

Ablation in OR

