**Week 28**

Assess for residual disease: HRA + biopsy + pap smear + HPV genotyping

No detection of AIN2/3 lesion by biopsy + anal pap smear

Detection of AIN2/3 lesion by biopsy + anal pap smear

Ablation in OR***

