The primary strategy to decrease disease burden in HPV-infected individuals is to intervene when premalignant anal disease, AIN2/3, is detected prior to the development of ASCC. All treatments for AIN2/3 are ablative and include electrocauterization/fulguration, hyfrecation, laser vaporization. Because they involve tissue destruction, all current therapeutic options have the potential for adverse sequelae, such as pain, fecal incontinence, and anal stenosis. Furthermore, these ablative techniques are not curative. Recurrences are common; in HIV-seronegative persons treated with ablation, recurrence is as high as 50% within one year of ablation.[2](#_ENREF_2) In HIV-positive individuals, recurrence rates are as high as 68%.[10](#_ENREF_10) An effective topical intervention that targets the underlying cause, HPV, would obviate the need for surgery and prevent progression to ASCC.

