## Duration of Follow Up

Patients will be followed for a total of 40 weeks from the first day of administration of the study drug or until death, whichever occurs first. Patients removed from study treatment for unacceptable adverse event(s) will be followed until resolution or stabilization of the adverse event.

Please see the schematic diagram for treatment follow-up as outlined in the Protocol Synopsis section.

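### Section 8.3.8 sends all residual disease visible on HRA at weeks 16 and 28 to ablation, while the schema lists ablation under no improvement (week 16) and detected AIN2/3 (week 28)

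*Protocol*

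**What the plan says.** Protocol Section 8.3.8 states the ablation rule as a conditional instruction: "At weeks 16 and 28, if there is residual disease visualized by HRA, patients will undergo repeat HRA with surgical ablation". The trigger is disease seen on HRA. Nothing is asked about change in size, change in grade, or biopsy confirmation of AIN2/3. A frozen section for AIN2/3 is mentioned, but only where possible and once the patient is in the operating room.

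Section 5.4 directs the reader elsewhere for follow-up: "Please see the schematic diagram for treatment follow-up as outlined in the Protocol Synopsis section". The week 16 box of that schema has one branch headed "Some improvement observed", described by lesion size on office HRA and by a lower AIN grade on biopsy and smear. A second branch is for no improvement, and ablation in the operating room is listed directly after it. The week 28 box splits on whether or not there is "detection of AIN2/3 lesion by biopsy + anal pap smear", and ablation is listed after the positive branch. Section 7 repeats the same boxes.

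Three other places touch on ablation:
- Section 8.2, Table 1, has a row for excision if needed: "Can take place any time after week 16 HRA".
- The synopsis footnote on timing says "a postoperative visit will be done 4 weeks after ablation, i.e. either on week 20 or on week 32".
- Section 6 adds ablation for disease progression at an interval visit.

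**The concern.** A lesion that has shrunk but can still be seen on HRA, or that has gone from AIN3 to AIN2, meets the 8.3.8 trigger and also falls in the schema's improvement branch. The same patient is operated on at week 16 under one text and observed to week 28 under the other. Two institutions work from this protocol and could read it differently.

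Two things are at stake. The first is surgery that the schema would defer and might avoid; Section 2.1 says of ablation that "all current therapeutic options have the potential for adverse sequelae, such as pain, fecal incontinence, and anal stenosis". The second is a secondary objective. Section 1.2 measures regression at weeks 16, 28 and 40, and once a partial responder is ablated at week 16, regression attributable to artesunate at weeks 28 and 40 can no longer be observed in that patient.

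**Working it through.** There is no stated figure to reproduce. The check sets the two rules side by side and then sizes one affected patient.

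**The two rules applied to the same patients**

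| Finding | Section 8.3.8 | Schema |
|---|---|---|
| Week 16: lesion smaller or lower grade, still visible | Ablate | Improvement branch; ablation not listed there |
| Week 16: visible lesion, no improvement | Ablate | Ablate |
| Week 28: visible AIN1, no AIN2/3 | Ablate | No-AIN2/3 branch; ablation not listed there |
| Week 28: AIN2/3 visible and detected | Ablate | Ablate |

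The first and third rows conflict. In the third row, the patient already counts as regressed under Section 1.2, where AIN1 qualifies.

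**Does other text settle it?** The footnote's postoperative visits imply ablation at 20 − 4 = week 16 or 32 − 4 = week 28, which fits both rules. Table 1 gives timing but no criterion. Section 6 covers progression only. None of them resolves the conflict.

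**What is unaffected.** Section 5.2 ends the DLT period at week 3 (2 cycles) or week 5 (3 cycles), well before week 16, so DLT assessment and the MTD are not touched. The week 16 assessment precedes any ablation it triggers.

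**Size for one late regressor.** Take a patient who would regress between weeks 16 and 28 but is ablated at week 16, and assume that regression after ablation is not credited to the drug. The denominator is not settled:
- Section 14.1 describes adding patients to the MTD cohort up to a total of 12, so one patient is 1/12 = 8.3 percentage points.
- The synopsis and Sections 5.1 and 5.2 describe an expansion cohort of 12 at the MTD. Added to the 6 patients on which the MTD rule rests, that gives 6 + 12 = 18, so one patient is 1/18 = 5.6 points.

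For scale, the exact (Clopper-Pearson) 95% interval at n = 12 is 0 to 26.5% for 0/12, since 1 − 0.025^(1/12) = 0.265. For 6/12 it is 21.1% to 78.9%, a width of 57.8 points.

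**Timing.** For a partial responder whose AIN2/3 persists at week 28, week 40 falls 40 − 16 = 24 weeks after ablation under 8.3.8 and 40 − 28 = 12 weeks after it under the schema. This takes ablation to occur at the visit week. The extra wait under the schema is 28 − 16 = 12 weeks. With the ±2 week visit windows in Table 1, it runs from 26 − 18 = 8 to 30 − 14 = 16 weeks.

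**The case against.** The strongest reply is that the schema's arrows are not visible in the text reviewed, and that the order of its boxes is not reliable: the week 6 box, for instance, comes after week 40. Section 8.3.8 also sits among descriptions of procedures, and the schema's own boxes open by assessing for residual disease. On that reading 8.3.8 is shorthand for the outcome of the assessment, and the schema supplies the branches. The frozen section for AIN2/3 suggests that suspected AIN2/3 is the disease 8.3.8 has in mind.

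Part of this stands. The branch-to-action links are inferred and should be confirmed against the figure, and the week 28 AIN1 conflict rests on the literal wording. The week 16 conflict remains on either reading. Limiting residual disease to AIN2/3 still leaves a smaller AIN2/3 lesion under both rules, and an improvement branch would serve no purpose if all visible disease were ablated.

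A second reply is that ablation is the standard of care, so 8.3.8 could be the deliberately cautious rule. A reader might infer that Section 5.4 makes the schema binding. It does not: it is a pointer under follow-up duration and states no order of precedence. That the schema is the intended rule is an inference from this pointer and from its appearing twice.

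A third reply is that the schema also ablates week 16 non-improvers, so later visits are confounded by surgery in any case. That is correct; rewording 8.3.8 narrows the problem and does not remove it.

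**Conclusion.** The inconsistency is real and minor. As worded, 8.3.8 and the schema assign different management to week 16 partial responders and to visible AIN1 at week 28, and nothing else in the protocol decides between them. Confidence is medium, because the branches are read from labels without arrows.

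The size is 5.6 to 8.3 points of the week 28 regression proportion for each affected late regressor, and only if regression after ablation is not credited to the drug. Section 14.3 does not say how such patients are counted, and that can be left to an analysis plan. A reader might infer that the week 28 result is biased by this amount. The documents do not support that: they give no basis for the number of such patients, which may be zero, and the efficacy analysis is descriptive. Nor do they support a threat to the primary objective. Week 40 status could also differ, since Section 2.1 reports recurrence after ablation, but that effect cannot be quantified from the protocol.

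**What to change.** Reword Section 8.3.8 to the schema, once the investigators have confirmed the branches against the figure:
- Week 16: ablate for no improvement in lesion size or AIN grade, or for progression (as Section 6 already requires). The investigators should state whether improvement in one of the two is enough, since the schema does not say.
- Week 28: ablate if AIN2/3 is detected.
- State that AIN1 alone is not a trigger.
- Record the trigger and the date of ablation on the CRF.

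The cost is wording in one section and a CRF entry, with no added visits or procedures. The downside is that partial responders with persisting AIN2/3 wait about 12 more weeks for ablation. The schema already provides for this, and the synopsis lets patients choose surgery at any time. If the investigators intend 8.3.8 to govern instead, the schema should be changed in both places.
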